### 2.6. Randomization and Allocation Concealment

The randomization will be by blocks, and this will be divided by the number of subjects in each block (health center). Six primary health centers will participate, so that, in each block/health center, the sample will be 32 subjects (16 IG and 16 CG). This would be a total of 192 participants, which would cover the calculated sample size of 182 subjects).

A list of random numbers generated by the EpiInfo 7.1 programme will be used to randomly assign participants to groups and to minimize the variation in external factors that can affect the comparison. The randomization method will be masked; therefore, the researchers who perform the randomization will not know to which group each subject will be assigned. To mask the randomization process, sealed and opaque envelopes will be sequentially numbered.

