### 2.5. Sample Size

For the calculation of the sample size, a primary outcome measure, quality of life (QOL), was selected [28]. The QOL measure used for this study goes from 1 (extremely poor) to 10 (excellent). A Cohen’s d of 0.4 (effect size) was established, taking into account a difference in quality of life of 0.75 and a standard deviation of 1.8. This effect size has been established, taking into account previous studies [29], and is expected to occur over time, after the intervention. For its part, the type I error has been set at 5% and the type II error at 20%. According to these parameters, 91 subjects will be needed in the intervention group (IG) and 91 subjects in the control group (CG). Depending on the proportion of losses that may occur, the sample size will be increased, calculating an adjusted sample size. In the event that the pilot study suggests making modifications in the calculation of the sample size due to a re-estimation of the effect size, the appropriate corrections will be made before beginning the study. In this study, sample size estimation was performed using the Granmo Calculator, available online in several languages (https://www.imim.cat/ofertadeserveis/software-public/granmo/) (accessed on 15 May 2022.).

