### 2.10. Data Analysis

The statistical analysis of the data will consist of a descriptive presentation of the parameters analyzed in the CUMACA-M programme. Continuous variables will be described as the mean and standard deviation. Categorical variables will be presented as frequencies and percentages. Subsequently, after assessing the normality of the data, corresponding inferential analyses will be performed. During the first stage, an assessment of the homogeneity of the groups (IG and CG) will be carried out by comparing the outcome variables (QOL and self-efficacy), sociodemographic variables, and clinical variables. For this, Student’s t test will be used for the quantitative variables, the chi-square test for the nominal or dichotomous variables (with the corresponding Fisher’s correction, if necessary), and the Wilcoxon test for variables of an ordinal nature. In a second stage, the differences in the outcome variables between the 2 groups (IG and CG) over time (T0, T1, T2, and T3) will be analyzed using multivariate analysis (MANOVA), in which the “group” factors will be incorporated and “time”, as well as the interaction between the 2. In all cases, the significance level will be set at 0.05. The data will be analyzed with the help of SPSS 24.0 software (IBM, Chicago, IL, USA, 2022)).

The intervention will be considered effective if the two variables evaluated (quality of life and self-efficacy) show results of improvement in the intervention group compared to the control group.

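### Randomisation is balanced within health centre but the stated model has no centre term; if centre is prognostic, between-arm comparisons of scores lose a little precision

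*Protocol article*

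**What the plan says.** Section 2.6 of the protocol article (Randomization and Allocation Concealment) blocks the allocation by centre: "The randomization will be by blocks, and this will be divided by the number of subjects in each block (health center". It then fixes the split: "in each block/health center, the sample will be 32 subjects (16 IG and 16 CG", in six centres. The section adds up the result: "This would be a total of 192 participants, which would cover the calculated sample size of 182 subjects".

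Section 2.10 (Data Analysis) states that the outcomes over T0 to T3 "will be analyzed using multivariate analysis (MANOVA", a model "in which the “group” factors will be incorporated and “time”, as well as the interaction between the 2". Health centre is not among the named factors, and no other section says that the analysis accounts for it.

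Section 2.3 (Settings) allows further centres to be brought in if recruitment falls short.

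**The concern.** When arms are balanced within each centre, every centre contributes equally to both arms. Whatever separates one centre from another (case mix, or how the nursing consultation is run) then drops out of the difference between arms. A model without centre does not know this. It counts between-centre variation as noise and reports a standard error larger than the true sampling error of the difference. Intervals come out too wide, the test rejects less often than its nominal 5%, and some of the precision bought by blocking is lost.

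Section 2.10 calls the programme effective only if both quality of life and self-efficacy improve, so the loss could fall on two outcomes. If centres are added and fill unevenly, exact balance may also fail, and a model without centre leaves any resulting imbalance unadjusted.

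**Working it through.** **Inputs.** Section 2.5: "taking into account a difference in quality of life of 0.75 and a standard deviation of 1.8", 5% type I and 20% type II error, 91 per arm. Section 2.6: six centres, 16 + 16 in each, so 96 per arm. Sidedness is not stated; two-sided is assumed because it reproduces the stated size. The centre ICC (the share of score variance lying between centres) is not given, so a range is assumed.

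**Step 1: the plan's own figure.** n per arm = 2 × (1.96 + 0.8416)² × (1.8/0.75)² = 2 × 7.849 × 5.76 = 90.4, rounded up to 91. It reproduces.

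**Step 2: standard errors at 96 per arm.**
- Reported without centre: 1.8 × √(2/96) = 0.2598. A finite-sample factor of 96/95 on the between-centre part lifts this to 0.2599 at ICC 0.05 and 0.10.
- True, under exact 16:16 balance: 1.8 × √(2/96) × √(1 − ICC) = 0.2585, 0.2532 and 0.2465 at ICC 0.01, 0.05 and 0.10.
- Ratio of reported to true: 1/√(1 − ICC).

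**Step 3: size and power.**
- Size without centre = 2 × [1 − Φ(1.96 × ratio)].
- Power without centre = Φ[(0.75 − 1.96 × reported SE)/true SE].
- Power with centre = Φ[0.75/true SE − 1.96].

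| Assumed ICC | SE ratio | Size without centre | Power without centre | Power with centre |
|---|---|---|---|---|
| 0 | 1.000 | 5.0% | 82.3% | 82.3% |
| 0.01 | 1.005 | 4.9% | 82.4% | 82.7% |
| 0.05 | 1.026 | 4.4% | 82.9% | 84.2% |
| 0.10 | 1.054 | 3.9% | 83.5% | 86.1% |

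For example, at ICC 0.05 without centre: (0.75 − 1.96 × 0.2599)/0.2532 = 0.950, and Φ(0.950) = 82.9%. With centre: 0.75/0.2532 − 1.96 = 1.002, and Φ(1.002) = 84.2%.

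**Step 4: simulation of a single follow-up score** (six centres of 32; 20,000 runs for size, 8,000 for power).

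| Assumed ICC | SE ratio | Size without / with centre | Power without / with centre |
|---|---|---|---|
| 0.01 | 1.002 | 4.8% / 4.8% | 82.2% / 82.4% |
| 0.05 | 1.020 | 4.5% / 5.0% | 83.0% / 84.1% |
| 0.10 | 1.044 | 3.9% / 4.7% | 83.3% / 85.6% |

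The simulated ratios are slightly below the formula. The simulation draws six centres at random, and their realised spread averages 5/6 of the between-centre variance. Allowing for this, √[1 + ICC/(1 − ICC) × (96/95) × (5/6)] gives 1.022 at 0.05 and 1.046 at 0.10, in agreement with the simulation.

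**Step 5: the group-by-time contrast.** Change from T0 to a follow-up visit was simulated with an assumed within-person correlation of 0.6. With a centre effect that is constant over time, the SE ratio was 1.000, 0.999 and 1.000 at ICC 0.01, 0.05 and 0.10, because the effect subtracts out. With 5% of the variance as a centre effect specific to each visit, the ratio was 1.050. Size was then 3.8% without centre against 4.9% with it, and power 88.5% against 90.5%.

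**The case against.** The strongest reply is that the natural test of effectiveness here is group-by-time. The model includes T0, and section 2.5 expects the effect to emerge over time. Stable centre differences cancel from that contrast, so the tables in steps 3 and 4 do not describe it. This stands: those figures are for the group effect or group at a single visit. For group-by-time an excess needs centre effects that shift between visits, and the article gives no evidence on that either way.

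A second reply is that centre effects may be small. All the centres lie in one region and the intervention is delivered through a web and mobile application. This too is fair, and it is why the result has to be stated as conditional on an unknown ICC.

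A third is that a condensed article may leave stratification factors to an analysis plan that is not shown. This stands only in part. Section 2.10 names the factors of the model, so a stated model fails to reflect a stated design. It does not say that the list is complete, which is a further reason to rate the point low.

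Two stronger readings should be set aside. A reader might infer that ignoring centre makes standard errors too small and raises false positives, as in a cluster-randomised trial. But women are randomised individually within centres, so the direction is the reverse. A reader might also set power with centre at 91 per arm (80.2%, 81.8% and 83.8% at ICC 0.01, 0.05 and 0.10) against a fixed 80% without it. That overstates the gain, because the unadjusted estimate has the same smaller true variance and its power also rises: 79.9%, 80.4% and 81.1%. The gains are about 0.3, 1.4 and 2.7 points.

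**Conclusion.** The point holds in a conditional and limited form. The stated model does not reflect the stated blocking. If centre is prognostic, between-arm comparisons of scores carry standard errors that are too large, by roughly 0.5% to 5.4% over the assumed ICC range of 0.01 to 0.10, and the power forgone at 96 per arm is about 0.3 to 2.6 points. The documents do not support saying that the standard errors are too large without qualification: at ICC zero nothing is lost, and for group-by-time nothing is lost unless centre effects vary by visit.

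The figures assume a two-sided test, a total standard deviation of 1.8, exact 16:16 balance and no losses. Under those assumptions power at the planned 192 exceeds 80% with or without centre. Neither bias nor an inflated type I error follows. Severity is low.

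**What to change.** In section 2.10, add health centre as a fixed between-subject factor, together with its interaction with time, to the models for quality of life and for self-efficacy, and fix this before outcome data are seen. The interaction with time is needed because a centre main effect alone does nothing for the group-by-time test. State that any centre added under section 2.3 enters the factor as a further level.

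The cost is small. Centre must already be known in order to allocate. With six centres the factor takes 5 degrees of freedom, so the between-subject error falls from 190 to 185. In the univariate repeated-measures form with four visits, centre-by-time takes a further 5 × 3 = 15 of the 190 × 3 = 570 within-subject error degrees of freedom. Each added centre costs a little more. Sample size and data collection are unchanged.

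### The 192 women are set against a requirement not adjusted for losses, leaving room for 5.2% loss, and the planned MANOVA in its usual form would spend that margin on any missed questionnaire

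*Protocol article*

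**What the plan says.** Section 2.5 (Sample Size) bases the calculation on "a difference in quality of life of 0.75 and a standard deviation of 1.8", with type I error 5% and type II error 20%, and arrives at 91 women per group, 182 in all. No loss rate enters the calculation. The section then adds: "Depending on the proportion of losses that may occur, the sample size will be increased, calculating an adjusted sample size".

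Section 2.6 (Randomization and Allocation Concealment) sets 32 women at each of six centres, 16 per group, and concludes: "This would be a total of 192 participants, which would cover the calculated sample size of 182 subjects". Losses are not mentioned there.

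Section 2.10 (Data Analysis) says that group differences "over time (T0, T1, T2, and T3) will be analyzed using multivariate analysis (MANOVA"), with group, time and their interaction, in SPSS. It gives no rule for missed assessments.

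Under sections 2.8 and 2.9, baseline is collected face to face. The 3-, 6- and 9-month questionnaires are completed remotely after prompts by email and WhatsApp, and also through the web application in the intervention group. Section 2.11 says that the intervention group's questionnaires are built into the programme, while the control group uses a separate online tool.

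**The concern.** Section 2.6 compares women randomised with the number needed for analysis. Those two numbers are comparable only if almost nobody is lost. The adjustment promised one section earlier is not applied, and the surplus of 10 comes from multiplying 32 by 6, not from an assumed rate of loss.

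The named analysis makes the margin matter more. A classical repeated-measures MANOVA needs a complete set of scores from each woman. Unless missing scores are imputed, one missed questionnaire out of three removes her from the test along with the data she did provide.

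Two things are at stake. One is power. The other is bias: in the intervention group, answering the questionnaire means opening the programme, so full completion may follow use of the programme. Restricting the analysis to full completers could then select engaged users in one group and not in the other.

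**Working it through.** **Inputs.** Difference 0.75, SD 1.8, type I error 5%, type II error 20%, 91 per group required (section 2.5); 6 × 32 = 192, so 96 per group (section 2.6). Section 2.5 does not say whether the test is one- or two-sided. Two-sided is assumed because it reproduces 91, whereas one-sided gives 72. Loss rates are assumptions throughout, since the article gives none.

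**The plan's own figure.** n per group = 2 × [(1.960 + 0.842) × 1.8 / 0.75]² = 90.4, rounded up to 91. This matches. The effect size used is 0.75/1.8 = 0.417; the rounded 0.4 would give 99.

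**Margin.** (192 − 182)/192 = 10/192 = 5.2%, or 5 of 96 women per group.

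**Power as women are lost.** Two-sample comparison at d = 0.417 with n = 96 × (1 − loss) per group:

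| Loss (assumed) | n per group | Power, t-based | Power, normal approximation |
|---|---|---|---|
| 0% | 96 | 81.9% | 82.3% |
| 5.2% | 91 | 79.8% | 80.3% |
| 10% | 86.4 | 77.7% | 78.2% |
| 20% | 76.8 | 72.8% | 73.3% |
| 30% | 67.2 | 66.9% | 67.6% |

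Power crosses 80% at about 5% loss (t-based) or 6% (normal approximation).

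**If any missed visit excludes a woman.** Assume each of the three follow-ups is missed independently with the same probability q. The complete fraction is (1 − q)³.

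- q = 2%: 0.98³ = 94.1% complete, power about 80%.
- q = 5%: 0.95³ = 85.7% complete (82 per group), power about 76%.
- q = 10%: 0.90³ = 72.9% complete (70 per group), power about 69%.

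To stay within 5.2%, q must be below 1 − (182/192)^(1/3) = 1.8% per visit. Independence is the unfavourable case: if the same women miss several visits, fewer women are affected for a given q.

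**What baseline adjustment could recover.** With correlation r between baseline and follow-up, the effective d is 0.417/√(1 − r²). At 20% loss (76.8 per group), r = 0.3 gives d = 0.437 and power 77%; r = 0.5 gives d = 0.481 and power 84%. At 30% loss, r = 0.5 gives 79%. The article gives no such correlation. These figures show the effect of adjusting for baseline at one follow-up time. They do not measure the further gain from keeping women with partial follow-up.

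**The case against.** Four points can be made for the plan.

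*192 may not be final.* Section 2.5 commits to an increase for losses and to corrections after the pilot, section 2.3 allows new centres if the sample size is not reached, and section 2.6 is worded conditionally. This stands in part: the article does not settle on 192. But section 2.6 calls that number sufficient without the adjustment, and the trigger in section 2.3 does not clearly cover losses after randomisation. The sections still need reconciling.

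*Exclusion of incomplete cases is not written down.* Section 2.10 mentions neither complete cases nor a repeated-measures procedure. It could be read as time entered as a factor with the two outcomes as dependent variables, in which case a missed visit loses one record and not the woman. Imputation may be described in an analysis plan that is not shown. This stands, so the exclusion is a consequence of the method's usual form and not a stated rule. The absence of a missing-data rule from the article is not itself the point.

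*The power figures are not for the planned test.* They refer to an unadjusted two-group comparison, which is the plan's own basis. For a group-by-time multivariate test with 3 degrees of freedom, assuming compound symmetry and a constant 0.75 difference at all three follow-ups, 70 women per group give power of 70%, 81% and 91% at within-woman correlations of 0.5, 0.6 and 0.7, and 62% at 0.4. The MANOVA could therefore do better or worse than the table.

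*The tempting stronger reading.* A reader might infer that 80% power will be missed and that fewer than 182 women will be analysed. The article does not support this. It gives no expected loss, and on its own basis power stays at about 80% up to about 5–6% loss.

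**Conclusion.** The point holds in conditional form. Section 2.6 does not apply the loss adjustment that section 2.5 promises, and 192 tolerates exactly 5.2% loss. Beyond about 5–6% unusable data, power on the plan's own basis falls below 80%, reaching about 78%, 73% and 67% at 10%, 20% and 30%.

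That the margin is also used up by single missed questionnaires rests on the usual repeated-measures form of MANOVA without imputation. The risk of bias rests on the same condition and on completion being related to use of the programme. Neither loss nor bias is shown to occur. What is shown is that the plan claims sufficiency with almost no allowance, and names a method that, in its usual form, handles partial follow-up poorly.

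**What to change.** 1. In section 2.10, replace the MANOVA with a likelihood-based mixed model (SPSS MIXED), fitted separately for quality of life and self-efficacy. Use the T1–T3 scores as the response, with group, time, their interaction and the baseline score as fixed effects. Analyse women as randomised and keep every woman with at least one post-baseline score. The model uses partial follow-up under a missing-at-random assumption; it does not recover women with no follow-up, nor remove bias if missingness depends on unobserved scores.

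2. Reconcile sections 2.5 and 2.6. Replace the statement that 192 covers 182 with the loss that 192 tolerates (5.2%), and give the power at a stated, assumed loss rate. If the intention is to retain 91 per group, the adjustment in section 2.5 is 91/(1 − loss): 102 per group at 10%, 114 at 20% and 130 at 30%.

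**Cost.** The first change needs a different procedure in the same software and no new data. The second is wording if 192 is kept, with the drawback that the stated power may be less favourable. Baseline adjustment may recover it, but that depends on a correlation the article does not give, so it cannot be promised that no extra women are needed.

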### 2.7. Description of the CUMACA-M Intervention

The personalized digital intervention will be designed in web and mobile application format to facilitate access at any time and from any place, regardless of the device used (computer, tablet, or smartphone). As it is a personalized intervention with the use of different algorithms using artificial intelligence, participants will receive information adapted to their personal needs. As mentioned above, the contents will be developed from an exhaustive review of recommendations and clinical practice guidelines for the care of LS-BC and on the main needs of LS-BC (Phase I of the MRC). Subsequently, the content of the intervention will be agreed upon by a panel of multiprofessional experts from PHC and specialized care, as well as an LS-BC and a representative of an association supporting women with breast cancer.

These contents will be configured in different modules according to the areas identified as priority needs of the LS-BC (for example, fatigue module, lymphedema module, work activity module, and fear of recurrence module), and the principles of the educational intervention characteristic of PHC consultations will be followed (feedback methods, risk personalization, increased awareness, active learning, persuasive communication, goal setting, and actions) [30].

The main page of the digital intervention programme will show a personal record and a video on how to use the programme. The intervention will begin with a screening questionnaire that will measure several concepts that impact quality of life, such as fatigue, anxiety, fear of recurrence, or return to work. According to the responses, participants will receive personalized advice by means of artificial intelligence algorithms on which modules deserve more attention. The web application itself will integrate the measurement of outcome variables that will allow evaluation of the effectiveness of the intervention. The effective management of the topics identified for the intervention will ultimately improve the quality of life of the LS-BC.

In Phase II (feasibility and piloting), the pilot of the intervention will be carried out through a pre-experimental pretest–post-test design with a single group that will pilot the intervention and test the usability of the application to identify areas for improvement and introduce timely modifications.

### 2.8. Evaluation Measures

The independent variable will be the CUMACA-M programme, since it is expected that, after its application, there will be changes in the values of the dependent variables (see below). Measures of the variables of interest will be collected, both in the IG and in the CG, at the preintervention time (T0), at 3 months after the intervention (T1), at 6 months (T2), and at 9 months (T3).

The dependent variables analyzed will be quality of life (QOL) of cancer survivors (CS) and self-efficacy in the management of cancer sequelae.

Quality of Life—Cancer Survivors (QOL-CS scale, Spanish version): it will be used with cancer survivors in QOL [24] and its 41 items in the 4 domains of QOL (physical, psychological, social, and spiritual well-being) will be measured on a Likert-type scale from 1 (extremely poor) to 10 (excellent). The overall QOL-CS tool test–retest reliability was 0.89, with subscales of physical 0.88, psychological 0.88, social 0.81, and spiritual 0.90 [24]. Cronbach’s alpha coefficient is a measure of agreement between items and subscales. The analysis revealed an overall r = 0.93. Subscale alphas ranged from r = 0.71 for spiritual well-being, r = 0.77 for physical, r = 0.81 for social, and r = 0.89 for psychological. Cronbach’s alpha is 0.93. Subscale alphas ranged from 0.71 for spiritual well-being, 0.77 for physical, 0.81 for social, and 0.89 for psychological [24].

Self-Efficacy for Managing Chronic Disease 6-Item Scale (SEMCD−6, Spanish version): it will be used to assess self-efficacy in the management of cancer sequelae and promotion of healthy lifestyles [31]. It is structured into 6 items related to the control of symptoms, role performance, emotional state, and communication with health professionals. In this study, the Spanish version of the SEMCD will be used that is structured into 4 items compared to the 6 in the English version [31].

The sociodemographic data of the LS-BC (age, sex, marital status, educational level, and employment status) will be collected through an ad hoc questionnaire at the beginning of the intervention. Data on the medical history (type of breast cancer, type of treatments, time elapsed since the end of active cancer treatment, relapses, and comorbidities) and follow-up will be collected through the clinical history of the LS-BC.

At the end of the intervention, satisfaction with the care received (CUMACA-M programme for the IG and standard nursing care for the CG) will be measured through the Spanish version of the CSQ−8 Satisfaction Questionnaire [32]. Each of the 8 items has 5 response options (from very dissatisfied to very satisfied).

